##### Mapping

TMS mapping will be used to identify the motor cortical representation of the ECRB and assess corticomotor excitability, following a rapid and reliable procedure [58]. Rapid mapping will be performed over a 70 mm × 70 mm area flat grid within a neuronavigation display. The grid will be centered on the hotspot, extended +3.5 cm and −3.5 cm in the frontal (mediolateral) plane and +3.5 cm and −3.5 cm in the sagittal (anteroposterior) plane, and curved and superimposed on a scaled generic brain image and localized relative to Cz. The pseudorandom walk method will involve delivering 120 stimuli at 120% of day 0 rMT at randomized locations within the grid, with a minimum of 4-second interstimulus interval, ensuring an average density of 4 stimuli per cm² to achieve a dense distribution of stimulation sites for accurate interpolation and peak identification [59-61]. The neuronavigation display will be monitored to confirm even stimulus distribution and prevent consecutive stimulations from being too close [62].

Motor maps will be generated offline using a custom Python script (scipy.interpolate.griddata) with a triangular linear interpolation used to create a continuous surface map from 3D MNI stimulation coordinates and corresponding peak-to-peak MEP amplitudes, while trials with background EMG activity will be excluded. The resultant motor map will be divided into 2500 partitions, each assigned an interpolated MEP value based on the nearest acquired data. Map volume will be calculated following van de Ruit et al [62], although a 50-μV minimum threshold will be used instead of the “greater than 10% of the maximum MEP” threshold, to include more responses and minimize outlier influence [58].

##### Paired Pulse

Paired pulse TMS will be performed to assess the short-interval intracortical inhibition (SICI) and the intracortical facilitation (ICF) for the right ECRB muscle following a standardized protocol [63]. Each condition will be tested in 12 trials at interstimulus intervals of 2 ms for SICI and 13 ms for ICF. As previous studies have shown that muscle pain reduces MEP amplitude [11,64] and that the size of the test response influences SICI magnitude [65], a 0.3-0.4-mV test response will be selected to maintain consistency across visits, even if corticomotor excitability decreases due to pain. The conditioning stimulus will be set at 90% rMT. An additional 12 unconditioned test trials will be recorded, totaling 36 trials, which will be presented in pseudorandom order. MEP responses will be measured as peak-to-peak amplitudes, and conditioned responses will be expressed as a proportion of the unconditioned test response.

### Sensorimotor Integration

SEPs will be recorded following electrical stimulation of the radial nerve. The cathode (black negative electrode) will be positioned 1.5 cm radial to the dorsal tubercle of the radius, targeting the superficial branch of the radial nerve [66]. The anode (red positive electrode) will be placed over the tendinous area in the distal third of the forearm. Electrodes will be spaced 3 cm apart. The forearm will be supinated with slight wrist extension [67]. Two blocks of 500 stimuli of 1-ms square pulse duration at a frequency of 2 Hz will be delivered, and a randomized interstimulus interval of 20% (0.4‐0.6 seconds) will be programmed to reduce habituation. The perceptual threshold will be determined by starting with a low-intensity stimulus and gradually increasing it until the participant reports a sensation. The stimulation intensity for the experiment will be set just below pain threshold without creating muscle twitches. Two blocks of 500 stimuli will be delivered while ensuring that the participant remains relaxed and minimizes movement to reduce artifacts.

The same EEG setup and preparation will be used as for the PAF. Data from the 2 blocks of 500 stimuli will be analyzed to examine the N_20_-P_25_-N_33_ complex as a marker of early cortical processing of somatosensory input. Data will be processed using MATLAB, resampled to 500 Hz, and auxiliary physiological channels will be excluded. EEG will be rereferenced to the right mastoid electrodes (M2). Band-pass filtering will be applied from 0.5 to 40 Hz (zero-phase finite impulse response), followed by a 59‐61 Hz notch filter. Data will be epoched from −50‐+150-milliseconds around each stimulus onset and baseline-corrected using the prestimulus interval (−50‐0 ms). Artifact rejection will be proceeded in 2 stages: automated *z*-value thresholding (cutoff = 4, FieldTrip *ft_artifact_zvalue*), followed by optional interactive summary rejection (*ft_rejectvisual*). All rejected trials will be logged with their rejection stage.

SEP will be extracted at electrode C3, contralateral to the stimulated right wrist, as it overlies the primary somatosensory cortex generating the early cortical response [68]. The area for the N_20_–P_25_–N_33_ complex within a window of 18‐40 ms will be computed per trial [22].

### Cognitive Function and Related Brain Activity

It is hypothesized that motor behavior in response to pain is influenced by individual cognitive coping strategies toward threat. People typically adopt either a passive coping strategy, focusing on pain and avoiding movement, or an active coping strategy, focusing on task completion and problem-solving. Previous work has shown that during a cognitive task performed in pain, individuals naturally adopt one of these strategies, which impacts performance [69-73]. Passive coping is associated with worsening performance, while active coping improves it [71]. This project will be the first to explore how these cognitive strategies relate to motor behavior in pain.

MSIT is a cognitive task designed to probe conflict resolution and cognitive control by activating the anterior cingulate cortex and frontoparietal networks [74]. MSIT combined with EEG allows investigation of how cognitive load influences pain perception and how pain affects cognitive performance. The MSIT will be modified from the original version of the MSIT [75], will be run using PsychoPy (version 2025.2.1; Open Science Tools Ltd), and will include 2 levels of difficulty: “low load” and “high load” [76]. In both levels, participants will identify the number on the screen that differs from the other 2 characters. They will use their right index, middle, and ring fingers to press the corresponding buttons, labeled “1,” “2,” and “3” arranged from left to right on a separated 3-keys keyboard. The MSIT introduces cognitive conflict by manipulating spatial and size-related features. For the easy level, 2 of the 3 characters are identical, and the position of the target number aligns with its corresponding button on the response box (eg, “323” with the correct answer being “2”). For the difficult level, spatial and size conflicts are introduced, meaning the target number does not align spatially with its button (eg, “311” with the correct answer being “3”). Each stimulus will remain on the screen until the participant presses a button, after which there will be a 1.25-second delay before the next stimulus appears [77]. To minimize cognitive fatigue, the task will be divided into 4 blocks per difficulty level (4 low load +4 high load), with 30-second rest periods between blocks. The participant will first be offered a training session consisting of an easy block and then a difficult block (repeatable if the participant wishes), followed by 8 blocks of 24 random trials in the fixed order load low-high-low-high-low-high-low-high, each separated by 30-second rests. For visits on day +2 and day +4, a tight armband will be applied over the site of injection to generate pain approximately 3/10 if the pain is less than this value at rest. We will examine behavioral performance for the 2 levels of difficulty, focusing on accuracy, defined as the proportion of correct, and reaction time, defined as the elapsed time between stimulus onset and the participant’s motor response.

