## Methods

### Study Design

A prospective longitudinal experimental study will be conducted to follow healthy individuals from the first induction of pain (day 0), as it develops and is sustained (day +2 and day +4), until 5 days after complete resolution of pain (Figure 1). Ethical approval has been obtained from the University of Western Ontario (reference 2025-125757-103291, January 9, 2025).

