### NGF Injection

Repeated intramuscular injection of NGF induces progressive, persistent muscle pain that is mechanistically, functionally, and clinically relevant. Importantly, NGF induces a gradual onset of pain without tissue injury [91], mimicking key features of persistent musculoskeletal pain, including movement-evoked pain, spreading hyperalgesia, and functional limitation [92,93], which resolve spontaneously around 25 days after injections have ceased [39,94]. These characteristics make the NGF model a safe and clinically relevant approach to investigate the cortical mechanisms underlying pain-related motor behavior and its individual variability, as it replicates the time course, movement-evoked nature, and sensitization processes characteristic of persistent musculoskeletal pain.

After cleaning the skin with alcohol, a solution of recombinant human NGF (Active GMP Recombinant Human NGF Protein from Creative BioMart Inc) will be administered as a bolus injection of 5 μg, dissolved in 0.2 mL of sterile water, into the muscle belly of the right ECRB muscle at the end of visits on days 0 and day +2. The injection will be administered using a 1-mL syringe with a 27-gauge, 1-inch needle. The site of injection will be located 1 cm lateral to a point that is 5 cm distal to the lateral epicondyle, along a line connecting the lateral epicondyle to the midline of the wrist [39,95]. The participant’s upper limb will be supported on a table, with the elbow flexed to 90° and the forearm in pronation to ensure proper positioning and accessibility to the target area. A permanent marker will be used to circle the injection site to maintain consistent injection placement in the ECRB muscle throughout the visits. In order to ensure optimal effectiveness of the hyperalgesia, we will keep the NGF at a temperature of −80 °C until a few minutes before the injection [96].

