### Statistical Analysis

The analysis will be performed using growth curve modeling (GCMs) with the R software (R Core Team; R Foundation for Statistical Computing) for the 2 main outcomes [121]. Advantages to the use of GCM to examine our aim are as follows: (1) GCM enables consideration of the time-varying nature of both outcome (motor behavior) and the mechanistic (central nervous system) variables in response to pain; (2) GCM allows mechanistic variables to be simultaneously adjusted, permitting estimation of the unique contribution of each mechanism to motor behavior, as well as interaction between mechanisms; and (3) GCM can use unevenly spaced measurements and all available data, even in the presence of missing data at random. Thus, we will investigate whether mechanistic variables (and the interaction between them) at each time point, and the change between time points, predict motor behavior. To address individual variation in motor behavior, the model will use a 2-level nested structure. Level 1 will be the within-participant model and level 2 the between-participants model. The within-participant component allows each participant to have a unique motor behavior via random effects, and the between-participants component represents variation in motor behavior between individuals with similar mechanistic characteristics. The issue of controlling many covariates in statistical modeling will be addressed using modern adjustment techniques (eg, shrinkage estimation or exposure modeling) [122]. In addition, bootstrapping will be used to identify variables to be included in the final model [123]. Two models will be developed, 1 for kinematic movement variability and 1 for muscle synergies.

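### MSIT change from day 0 to day +2/+4 mixes practice with the response to pain, because the only pre-pain session is the first exposure and training is self-dosed

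*Protocol article*

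**What the plan says.** All places are in the Protocol article.

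- **Rationale (Cognitive Function and Related Brain Activity).** From prior work: "Passive coping is associated with worsening performance, while active coping improves it". The section says the project will relate these strategies to motor behavior. A passive cognitive response is a named part of the hypothesis in the Introduction.
- **Task (same section).** Participants are offered "a training session consisting of an easy block and then a difficult block (repeatable if the participant wishes". The scored part alternates low and high load and is specified in these words: "followed by 8 blocks of 24 random trials in the fixed order". Accuracy and reaction time are the measures. "For visits on day +2 and day +4, a tight armband will be applied over the site of injection" if resting pain is too low, so these are the painful MSIT sessions.
- **Timing (NGF Injection; Study Design).** Injections are given "at the end of visits on days 0 and day +2". Participants are followed "until 5 days after complete resolution of pain". There is one cohort, all injected; no sham or pain-free group is described.
- **Analysis (Sample Size; Statistical Analysis).** Four MSIT variables are listed as cognitive response. The models ask whether "mechanistic variables (and the interaction between them) at each time point, and the change between time points, predict motor behavior".
- **Contrast (Primary Outcomes: Motor Behavior, Overview).** The motor task has a separate familiarization at all visits, continued until accuracy is above 95%. The MSIT has no counterpart.

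**The concern.** Pain and experience with the task begin together in every participant. Day 0 is the first exposure to the MSIT, and both painful sessions come after at least one full session. Practice usually shortens reaction time, and shorter reaction time in pain is the direction the article associates with active coping. Practice can therefore hide a worsening caused by pain, or add to an improvement.

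The amount of training is also left to each participant, with no criterion and no mention of recording it. Starting points on the learning curve then differ between people for reasons unrelated to pain.

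At stake is the meaning of one family of predictors. If people differ in how much they learn, MSIT change partly ranks them by learning rate. That weakens the test of the coping hypothesis. It could also tie the predictor to traits, such as age, that may affect movement in their own right.

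**Working it through.** The plan gives no figure to reproduce on this point. The check orders the sessions, counts trials and then illustrates the size.

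**1. Order of sessions.** The first injection is at the end of day 0, so day 0 is session 1 and pain-free. Day +2 and day +4 are sessions 2 and 3, in pain. The post-resolution visit is session 4, pain-free, if the MSIT is run there. The schedule figure is not shown, so the MSIT at day 0 and at the fourth visit is inferred.

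**2. Exposure before day +2.** Scored trials: 8 × 24 = 192. The length of a training block is not stated. If it is also 24 (assumed), one round adds 2 × 24 = 48, giving 240.

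**3. Illustrative model (every value assumed).** For session k:

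log reaction time = −a·ln(k) + P (only when k = 2 or 3) + noise

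- P, the true pain response: mean 0, SD 5%, the same in both painful sessions.
- Noise: SD 3% per session.
- Learning exponent a, mean (SD): 0.05 (0.025), 0.10 (0.05), 0.15 (0.05), independent of P.

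**4. Day 0-based change = mean(sessions 2, 3) − session 1.**

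- Weight on a: (ln 2 + ln 3)/2 = (0.6931 + 1.0986)/2 = 0.8959.
- Noise variance: 9/2 + 9 = 13.5. Variance of P: 25.
- Correlation with P = 5/√(25 + 13.5 + (100 × SD of a × 0.8959)²).

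**5. Bracketed contrast = mean(sessions 2, 3) − mean(sessions 1, 4).**

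- Weight on a: 0.8959 − (ln 4)/2 = 0.8959 − 0.6931 = 0.2027. Ratio 0.2027/0.8959 = 0.226, so 77% of the practice component is removed on this curve.
- Noise variance: 9/2 + 9/2 = 9.
- Correlation with P = 5/√(25 + 9 + (100 × SD of a × 0.2027)²).

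| SD of a | Day 0-based change | Bracketed contrast |
|---|---|---|
| 0 (no practice, or the same gain for all) | 5/√38.5 = 0.81 | 5/√34 = 0.86 |
| 0.025 | 5/√(38.5 + 5.02) = 0.76 | 5/√(34 + 0.26) = 0.85 |
| 0.05 | 5/√(38.5 + 20.06) = 0.65 | 5/√(34 + 1.03) = 0.84 |

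The mean of a does not enter, so the second and third scenarios give the same result. A gain common to everyone does no harm to a continuous predictor; the loss from 0.81 is due to differences between people, which a visit term does not remove.

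**6. What the change score picks up instead.** Its correlation with a is −2.24/√43.52 = −0.34 for SD 0.025 and −4.48/√58.56 = −0.59 for SD 0.05. For the bracketed contrast it is −0.09 and −0.17.

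**7. Scale-free check.** Write change = P + G, with P of SD 1 and practice gain G of SD s. The correlation with P is 1/√(1 + s²): 1.00 at s = 0, 0.89 at s = 0.5 and 0.71 at s = 1.0. The pattern is the same.

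The models contain no term for optional training rounds, so the effect of unequal training is not quantified here.

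**The case against.** **No scoring rule is stated.** A reader might infer that anyone who improves is scored as an active coper. Under such a rule, the model above would show apparent improvement from day 0 to day +2 in 70% to 92% of participants, against a true 50%: Φ(3.47/√(25 + 18 + 3.00)) = Φ(0.51) = 0.70 in the first scenario and Φ(10.40/√(25 + 18 + 12.01)) = Φ(1.40) = 0.92 in the third. The documents do not support that reading. The sentence on passive and active coping reports earlier work as rationale. The plan lists accuracy and reaction time by load, without a cut at zero. How a derived score is coded may sit in an analysis plan that is not shown. This objection stands, and those percentages are no part of the conclusion.

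**Coping is also measured by questionnaire.** The Coping Strategies Questionnaire–Revised is a separate predictor, so the hypothesis does not rest on the MSIT alone. This is true, but it does not repair the MSIT variables.

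**Levels are used as well as change.** Also true. The confounding concerns the change part and any comparison of a painful session with day 0.

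**Part of the gain from bracketing is only noise averaging.** Without practice it already raises 0.81 to 0.86. In the SD 0.025 scenario, about half of the rise from 0.76 to 0.85 is of this kind.

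**Repeatable training may help.** It could bring slow starters nearer to plateau before scoring. This stands against a simple ban on repeats. The weakness is that the dose is neither uniform nor tied to a criterion. The article also does not say at which visits training is offered, so a dose that varies between visits cannot be asserted.

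**Conclusion.** The point holds as one of confounding. MSIT change from day 0 to day +2/+4 contains practice and the response to pain together, and practice acts in the direction associated with active coping. This follows from the injection timing, the single injected cohort and the training rule. An analysis plan cannot standardise training already given at the participant's discretion, or recover a dose that was not recorded.

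The size is unknown. Under the assumed curves the correlation with the true pain response is 0.65-0.76, against 0.81 without practice. The loss of about 0.05 to 0.15 depends mainly on how much people differ in learning, for which the documents give nothing. Only reaction time was modelled, not accuracy.

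The documents do not support the stronger claim that practice gain is scored as active coping, or that most participants would be classed as active.

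**What to change.** 1. **Training.** Replace the optional repeats with one MSIT training rule applied to everyone at every visit: either a fixed dose or a performance-plateau criterion, as the motor task already has. Log the rounds completed.
2. **Model.** Include visit or session, and state that the sign of raw MSIT change is not read as active or passive coping.
3. **Sensitivity analysis.** If the MSIT is run at the post-resolution visit, add mean(day +2, day +4) − mean(day 0, post-resolution), centred on the sample mean. Both pairs have mean session number 2.5, so a linear practice trend cancels.

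**Cost.** One change to the task procedure, one logged field and one derived variable. At the last report 26 of 150 participants were enrolled, so most of the sample would benefit; the training dose of those 26 may be unrecorded.

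**Limits.** The bracketed score needs the fourth visit and assumes performance has recovered by then. It cancels only a linear trend (23% of the practice component remains on the curve above). The fourth visit may come weeks later, so retention may differ. The score also reduces a time-varying predictor to one value per person and uses later data to explain earlier motor behavior, which fits poorly with the temporal-precedence aim in Comparison With Prior Work. It therefore belongs in a sensitivity analysis and should not define the predictor.

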### Pain Modulation

Central sensitization, defined as an increased sensitivity of spinal and cortical neurons, and impaired descending pain modulation are key mechanisms influencing motor behavior in pain. These changes may interfere with the link between pain experience and motor behavior, as movement recovery may not reflect tissue healing [78]. Central sensitization can sustain pain beyond peripheral injury and interfere with the analgesic effects of movement. Moreover, it may compete with motor learning processes, potentially impairing motor adaptation [79]. While animal and human studies suggest a relationship between central sensitization and altered motor behavior, evidence remains limited [80-84].

CPM will be used to assess the inhibitory pain mechanisms, using 2 different types of test stimuli according to guidelines [85-87]. In our study, this assessment will involve measuring changes in both heat pain thresholds (HPTs) and pressure pain thresholds (PPTs) through 3 consecutive measurements, conducted twice and separated by a conditioned stimulus to activate endogenous pain modulation mechanisms [88].

The HPTs will be determined using a thermode (TCS-II, QST.Lab) equipped with a 4.5 cm² rectangular probe (T09). First, participants will undergo a familiarization phase with the thermode: holding the thermode in the palm of their hand and experiencing the temperature rise. Starting from a baseline temperature of 32 °C, thermal stimuli will be applied on the proximal third of the anterior surface of the right forearm of the participants with a gradual increase of 1 °C per second until the participant reports the first sensation of pain by pressing a response button. The temperature at this moment will be recorded as the HPTs. To ensure reliability, 3 consecutive measurements will be performed, and the mean value will be calculated and will be used for analysis. After each trial, the temperature will return to baseline in less than 1 second. Safety cutoff temperatures will be set at 50 °C to prevent tissue damage.

The PPTs will be assessed using a pressure algometer (Mxmoonfree ZMF-300N Portable Digital) equipped with a flat metallic round tip of 1.4 cm in diameter by exerting a constant pressure of 50 kPa per second (approximately 0.5 kg/cm^2^ s). During the assessment, the participants’ forearm will be placed on a table while an examiner will exert pressure perpendicular to the skin. Participants will be asked to say “stop” to signal when the sensation changes from pressure to pain. When the participant responded “stop,” the pressure will stop, the device will be removed from the skin, and the pressure value recorded. Three recordings will be made and averaged (1-minute intervals) over the right ECRB (on injection site) and used for analysis.

Both HPTs and PPTs will be assessed before and directly after a conditioning cold pressor test (CPT) in balanced order to allow us to measure several excitatory and inhibitory pain mechanisms. The CPT will be administered by immersing the participant’s left forearm in cold water at 10 °C with a water flow for 2 minutes [89].

The magnitude of CPM will be calculated by subtracting the average HPTs and PPTs measured after the CPT stimulus from those recorded before the CPT stimulus (pre-post). Therefore, a negative value will indicate pain inhibition (CPM response), while a positive value will suggest pain facilitation [90].

